We will evaluate the efficacy of Text4Hope with the reductions of perceived stress, anxiety, and depression at 6 weeks and 12 weeks. Data analysis will include the standard use of parametric and nonparametric techniques (eg, within-subject general linear models), including multiple comparison Type 1 error corrections. Power analysis with effect sizes based on [name] group research publications [26-28,36,37] indicates a sufficient effect size for the expected Text4Hope program subscriber sample size. As the sample size for the data set generated from this project will be large, in addition to the conventional statistics used in these projects, we plan to adopt a “big data” analysis approach to examine data-driven patterns. Using machine learning and data mining methods, we expect to capture the most powerful window on differences and high-order sets of potential interactions. With our program targeting 300,000 Canadians to self-subscribe, with an expected 60,000 completing the survey, we are confident that this project has adequate power for our basic cross-sectional approach. We will develop predictive models using baseline measurements (features) and machine learning algorithms (eg, the least absolute shrinkage and selection operator [LASSO], support vector regression [SVR], and random forest regression, etc [38-40]) to predict the efficacy of our intervention at 6 and 12 weeks, as measured by the change in assessment scores (eg, GAD-7, PHQ-9) compared to the baseline. We will perform a 10-fold cross-validation to evaluate the performance of the models. During cross-validation, the data will be randomly segmented into 10 folds, with each fold containing 10% of the data. For each iteration, 1 fold will be left out as the testing data and the remaining 9 will be the training data. Within each training session, another internal 10-fold cross-validation will be used to select the best features, algorithm, and corresponding hyperparameters as the model to be trained on this specific training session. The selected model in the training data will then be applied to the testing data. This procedure is crucial for predictive tools as the data being tested has never been seen in any way by the model. The performance of the models will be evaluated using the Pearson correlation between the predicted and actual reduction of the outcome measures.

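### Pearson correlation, the only performance measure named for the prediction models, cannot show bias, miscalibration or gain over predicting the average

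*Protocol article*

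**What the plan says.** The machine-learning plan is in the Results section of the protocol article. The models are meant "to predict the efficacy of our intervention at 6 and 12 weeks, as measured by the change in assessment scores", so the target is an amount of change in scale points and not a ranking of respondents. The candidate algorithms are LASSO, "support vector regression [SVR], and random forest regression, etc".

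Validation is nested. For the outer loop, "During cross-validation, the data will be randomly segmented into 10 folds, with each fold containing 10% of the data". Within each training set, "another internal 10-fold cross-validation will be used to select the best features, algorithm, and corresponding hyperparameters". The criterion that defines best in that inner loop is not named.

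For the outer loop the measure is stated: "The performance of the models will be evaluated using the Pearson correlation between the predicted and actual reduction of the outcome measures". The article mentions no RMSE, MAE, bias, calibration slope, out-of-sample R-squared or comparison with a mean-only prediction.

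**The concern.** The measure does not match the target. Pearson r describes how closely predicted and actual changes follow a straight line, whatever the intercept and (positive) slope of that line. A prediction of change in scale points should also be right in level and spread, and r carries no information on either.

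There are two consequences. Two models with clearly different prediction error can be reported with the same performance. And the natural benchmark, giving everyone the average change, has no defined r, so r alone cannot tell a reader whether a model improves on having no model. If r were also the inner-loop criterion, the choice between algorithms would be blind to the same difference.

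**Working it through.** The article gives no expected r, and no mean or SD of the change scores, so there is no stated figure to reproduce. The algebra in steps 1 to 3 needs no such values. The numerical examples use assumed ones, labelled as such.

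**1. Invariance.** For predictions p, actual changes y, any constant a and any k > 0: corr(a + k·p, y) = corr(p, y). For a constant prediction the SD of p is zero, so the denominator of r is zero and r is undefined.

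**2. What a shift does to accuracy.** Take a calibrated prediction with correlation r and add a constant error b. Then MSE = SD²(1 − r²) + b², so R² against the mean is r² − (b/SD)². This falls below zero once |b| > r·SD. With an assumed SD of 5 points, that threshold is:
- r = 0.2: 1.0 point
- r = 0.3: 1.5 points
- r = 0.5: 2.5 points
- r = 0.7: 3.5 points

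A 2-point shift shows how the range matters: R² = 0.09 − 0.16 = −0.07 at r = 0.3, but 0.25 − 0.16 = +0.09 at r = 0.5. A simulation with n = 60,000 agreed (−0.070 and 0.085), with r unchanged by the shift (0.297 and 0.499). These shifts were imposed on finished predictions to illustrate the algebra; they are not forecasts of what the planned models will do.

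**3. What a change of spread does.** Multiplying the spread of a calibrated prediction by k gives R² = r²(2k − k²). This is positive for every k between 0 and 2 and negative only for k > 2.

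**4. Can a difference arise under 10-fold cross-validation itself?** This was simulated with n = 6,000. The outcome was 3 plus a linear predictor with coefficients 1, 0.8 and 0.5 on standard normal features, plus an exponential error of mean 4, centred at zero. The outcome variance is 1 + 0.64 + 0.25 + 16 = 17.89 (SD 4.23). Two fits were compared on out-of-fold predictions, with bias taken as predicted minus actual:

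| Fit | Pearson r | Bias (points) | R² |
|---|---|---|---|
| Squared error | 0.324 | 0.0 | 0.105 |
| Median (absolute error) | 0.326 | −1.25 | 0.019 |

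The formula in step 2 explains the gap: 0.326² − (1.25/4.23)² = 0.106 − 0.087 = 0.019. In RMSE this is √(17.89 × 0.895) = 4.00 against √(17.89 × 0.981) = 4.19, with √17.89 = 4.23 for the mean-only prediction. On r the median fit looks marginally better; on squared error it has lost most of its gain over the mean.

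The median fit stands in for SVR, which also does not use a squared-error loss. SVR itself was not fitted.

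**The case against.** The strongest reply is that the planned procedure limits how wrong level and spread can become. Training and test folds are random parts of one data set. A LASSO with an intercept, or a random forest averaging training outcomes, reproduces the training mean closely. With an assumed SD of 5, even a test fold of only 600 has a chance error in its mean of about 5/√600 = 0.2 points. This stands, and it rules out several stronger readings that a reader might infer:

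- **That the chosen models may well be worse than predicting the average.** Hand-made examples, such as adding 4 points or tripling the spread, do give negative R², but nothing in the plan would produce them. In the cross-validated check the unfavourable fit still had R² of +0.019, above the mean-only prediction.
- **That shrinkage in LASSO or SVR is the cause.** Shrinkage narrows the spread (k < 1), which by step 3 cannot alone make R² negative. At r = 0.45 and k = 1/3, R² = 0.2025 × (2/3 − 1/9) = +0.11.
- **That the shifting epidemic is the cause.** Random folds mix subscription dates, so out-of-fold RMSE and calibration would largely miss drift too. The Results section also plans to include infection, death and unemployment data in these models.
- **That subscribers would be promised too much improvement.** The article nowhere says that individual predictions go to subscribers or guide care. The bias in the check was also downward, that is, too little predicted improvement.

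A further reply is that a condensed article may leave extra metrics to a full plan. That has some force for the inner-loop criterion and for calibration detail. It does not remove the point, because the article states which measure judges performance, and that measure does not fit the stated target. Correlation remains a legitimate summary of whether baseline features relate to change; it is incomplete as a summary of prediction accuracy.

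**Conclusion.** The point holds as a minor improvement to a supplementary analysis. Pearson r, as the sole named measure, cannot reveal bias or miscalibration, nor show gain over predicting the mean. That follows from algebra alone. It is most plausible in practice for an algorithm without a squared-error loss, such as SVR, applied to skewed change scores. The size found (almost equal r, but 1.25 points of bias and R² of 0.019 instead of 0.105) depends on an assumed exponential error and on a median fit as stand-in for SVR. With symmetric change scores or squared-error fits, little or no such bias is expected.

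The primary outcome, change on the three scales, is analysed by conventional methods and is unaffected, and none of the four hypotheses is stated in terms of prediction performance. The expected sample ("with an expected 60,000 completing the survey") does not alter the conclusion, since the invariance of r holds at any size.

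**What to change.** Replace the sentence on model performance so that, from the out-of-fold predictions, the report gives:
- RMSE or MAE in scale points for each scale and time point;
- R-squared against the training-fold mean, so that zero means no gain over giving everyone the average;
- calibration intercept and slope;
- Pearson r as a supplement.

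Name the same error measure as the criterion in the inner loop that selects features, algorithm and hyperparameters. If MAE is chosen, it should not stand alone: absolute error favours a median fit, so the R-squared and calibration intercept are needed to show any bias in the mean.

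The cost is a sentence or two of text. The performance measures come from predictions the plan already produces. No new data are needed, and the folds and nesting stay as they are.

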## Discussion

The impact of the COVID-19 global pandemic on health, way of life, and psychological safety and wellbeing is difficult to overstate. The psychological impact on the general population, both during and after the crisis, requires the use of innovative techniques that can serve the high number of people requiring support, while respecting the need to maintain physical distancing.

The current protocol describes the use of mobile health technology as a convenient, cost-effective, and accessible means for implementing a population-level psychological intervention during the pandemic. This program is empirically supported by previous research results, showing good outcomes as well as high user satisfaction [26,27]. This project will evaluate outcomes with standardized, empirically validated questionnaires, and will also provide key information regarding prevalence rates of stress, anxiety, and depression in the Canadian population during the COVID-19 pandemic; demographic correlates of this distress; and outcome data related to a scalable population-level intervention. Information from this study will thus be critical for practitioners, as well as useful for informing policy and decision-making regarding psychological interventions during the COVID-19 pandemic. If Text4Hope is effective for the Canadian population, we will explore scale-up and national implementation, and will disseminate this program for adaptation for potential global use through the APEC Digital Hub for Mental Health [42].

Limitations of this protocol include a lack of baseline data on stress, anxiety, and depression levels before self-isolation measures were implemented in Alberta; this was unavoidable as our study was initiated shortly after quarantine and self-isolation measures were introduced. Nonresponse bias may also affect the expected results, as program subscribers are a sample of the population, not the entire population of the province. Nonrespondents may differ in a systematic way compared to respondents. For example, they may differ in their baseline level of mental wellness, be more (or less) affected by the pandemic, or have limitations in literacy or English fluency. In view of the limitations noted above, any prevalence estimates must be interpreted with caution, and compared to the conventional baseline of subsequent conventional prevalence estimates. The authors also note that this protocol does not include a control group and this raises the question of specificity concerning hypothesis 3, which concerns reductions in perceived stress, anxiety, and depressive symptoms. Previous RCT work from this group has demonstrated the efficacy of supportive SMS text messaging in intervention groups, compared to control groups that did not receive supportive text messages; instead, the control group received the same survey requests as the intervention group in addition to a single text message every 2 weeks, thanking them for participating in the study [26,37]. Given the intention to provide support to the catchment population of this study and the prior evidence for efficacy, it would be unethical to include a control group in the current protocol. Nevertheless, prior studies did include subscriber satisfaction surveys, as does this protocol, and that measure will provide evidence for engagement of the subscribers with the program (simply put, if subscribers ignored the text messages, it is highly unlikely that there would be positive satisfaction survey results). In the current health implementation context of this protocol, the comparison of changes in outcome measures in relation to comparison with effect sizes from our prior work (together with an assessment of the degree of correspondence of subscriber satisfaction survey responses to changes in our outcome measures) will be a good indicator of subscriber engagement in the absence of a control condition. Despite these limitations and possible bias factors, our protocol will provide useful data about the mental health characteristics of individuals in the early stages of the COVID-19 pandemic. We expect that our results will represent an important initial source of information for government and health care planners in determining the nature and quality of services required to address mental health challenges arising during this pandemic, as well as future pandemics that employ self-isolation or quarantine measures. Specifically, planning for and implementing virtual care programs, including supportive SMS text messages, may be a fruitful approach to supporting isolated or quarantined individuals. In addition, we expect the supportive SMS text messaging intervention to have a positive effect on mental well-being and we will be able to measure this well within the expected sample size.

## Abbreviations

COVID-19: coronavirus disease
GAD-7: Generalized Anxiety Disorder-7 scale
LASSO: least absolute shrinkage and selection operator
PHQ-9: Patient Health Questionnaire-9
RCT: randomized controlled trial
SARS-CoV-2: severe acute respiratory syndrome coronavirus 2
SVR: support vector regression
